# Memantine for Refractory Obsessive-Compulsive Disorder: Protocol for a Pragmatic, Double-blind, Randomized, Parallel-Group, Placebo-Controlled, Monocenter Trial

**DOI:** 10.2196/39223

**Published:** 2023-05-11

**Keywords:** obsessive-compulsive disorder, refractory patients, antiglutamatergic agents, glutamate, augmentation medication, memantine, double blind, parallel group, placebo, OCD, psychiatric, distress, symptoms, neuropsychiatric, disability, overactivity, drug, treatment, Alzheimer, cognitive, titration, medication, mental health, psychiatric disorder

## Abstract

**Background:**

Obsessive-compulsive disorder (OCD) is a psychiatric syndrome characterized by unwanted and repetitive thoughts and repeated ritualistic compulsions for decreasing distress. Symptoms can cause severe distress and functional impairment. OCD affects 2% to 3% of the population and is ranked within the 10 leading neuropsychiatric causes of disability. Cortico-striatal-thalamo-cortical circuitry dysfunction has been implicated in OCD, including altered brain activation and connectivity. Complex glutamatergic signaling dysregulation within cortico-striatal circuitry has been proposed in OCD. Data obtained by several studies indicate reduced glutamatergic concentrations in the anterior cingulate cortex, combined with overactive glutamatergic signaling in the striatum and orbitofrontal cortex. A growing number of randomized controlled trials have assessed the utility of different glutamate-modulating drugs as augmentation medications or monotherapies for OCD, including refractory OCD. However, there are relevant variations among studies in terms of patients’ treatment resistance, comorbidity, age, and gender. At present, 4 randomized controlled trials are available on the efficacy of memantine as an augmentation medication for refractory OCD.

**Objective:**

Our study’s main purpose is to conduct a double-blind, randomized, parallel-group, placebo-controlled, monocenter trial to assess the efficacy and safety of memantine as an augmentative agent to a selective serotonin reuptake inhibitor in the treatment of moderate to severe OCD. The study’s second aim is to evaluate the effect of memantine on cognitive functions in patients with OCD. The third aim is to investigate if responses to memantine are modulated by variables such as gender, symptom subtypes, and the duration of untreated illness.

**Methods:**

Investigators intend to conduct a double-blind, randomized, parallel-group, placebo-controlled, monocenter trial to assess the efficacy and safety of memantine as an augmentative agent to a selective serotonin reuptake inhibitor in the treatment of patients affected by severe refractory OCD. Participants will be rated via the Yale-Brown Obsessive Compulsive Scale at baseline and at 2, 4, 6, 8, 10, and 12 months. During the screening period and T4 and T6 follow-up visits, all participants will undergo an extensive neuropsychological evaluation. The 52-week study duration will consist of 4 distinct periods, including memantine titration and follow-up periods.

**Results:**

Recruitment has not yet started. The study will be conducted from June 2023 to December 2024. Results are expected to be available in January 2025. Throughout the slow-titration period, we will observe the minimum effective dose of memantine, and the follow-up procedure will detail its residual efficacy after drug withdrawal.

**Conclusions:**

The innovation of this research proposal is not limited to the evaluation of the efficacy and safety of memantine as an augmentation medication for OCD. We will also test if memantine acts as a pure antiobsessive medication or if memantine’s ability to improve concentration and attention mimics an antiobsessive effect.

**Trial Registration:**

ClinicalTrials.gov NCT05015595; https://clinicaltrials.gov/ct2/show/NCT05015595

**International Registered Report Identifier (IRRID):**

PRR1-10.2196/39223

## Introduction

### Background

Obsessive-compulsive disorder (OCD) is one of the most disabling neuropsychiatric disorders, characterized by repetitive and intrusive thoughts (obsessions) and repeated ritualistic behaviors (compulsions) that are performed by affected individuals to decrease distress [1]. It is estimated that 2.5% to 3% of the general population are affected by OCD [2], which has some sex-related features [3]. Moreover, in the last decade, evidence suggests significant neuropsychological deficits—independent of severity, comorbidity, and medication—in patients with OCD [4,5]. Several studies suggest impairments in executive function, processing speed, sustained attention, and nonverbal memory [6-11].

Prior to the *Diagnostic and Statistical Manual of Mental Disorders, Fifth Edition* (DSM-5) [12], OCD was included as an anxiety disorder because patients commonly reported anxiety as a symptom [13]. However, in the DSM-5, OCD was moved to its own distinct section—*Obsessive-Compulsive and Related Disorders*—because the condition was considered to be more closely related to other disorders [14].

Typically, OCD is determined by obsessions (irrational beliefs) and compulsions that are rational avoidance responses activated by these irrational beliefs. Recent data [15,16] instead suggest that the mechanism underlying OCD can be found in an interference in the balance between the habit learning system and the goal-directed system. The habit learning system is founded on historical information, independent of past rewards, potentially resulting in behavioral inflexibility even in light of rapid changes in the environment. On the other hand, the goal-directed system applies control over habits in response to changes, including changes in response to the assessment of actions and outcomes. A study conducted by Voon and colleagues [17] found that patients with OCD made choices generally based on a model-free approach (habit learning system) rather than a model based on a goal-directed system.

In the current habit hypothesis of compulsivity, compulsions result from a deficit of goal-directed actions, rather than being driven by irrational beliefs. In line with this much more behavioral account of the disorder, OCD was inserted in the new *Obsessive-Compulsive and Related Disorders* chapter of the DSM-5.

Recurrent circuits that connect the cerebral cortex to the basal ganglia, which are termed *cortico-striatal-thalamo-cortical circuitry* (CSTC) *loops*, are involved in habits. CSTC dysfunctions, as structural abnormalities, alter brain activation and connectivity [18,19] and seem to be implicated in OCD. According to this hypothesis, the hyperactive or hyperconnected CSTC loops are self-exciting in a runaway positive feedback loop [20,21], resulting in the need to perform compulsions, which in turn reinforces habits and increases the urge to perform compulsions [22].

The primary neurotransmitter involved in the CSTC model of OCD is glutamate [23]; it also has a fundamental role in neuronal plasticity, learning, and memory [24]. Excessive levels of glutamate in the brain area can stimulate glutamate receptors, resulting in hyperactivity or even excitotoxicity in neurons; in pathological conditions, glutamate can act as a neuronal excitotoxin, resulting in rapid or late neurotoxicity [25].

In support of this hypothesis, a large mega-analysis and meta-analysis of imaging data found age-related changes in brain structures, suggesting that OCD is underpinned by complex, nonlinear neurodevelopmental mechanisms [26,27].

The pathophysiology of OCD indicates aberrant glutamatergic signaling, with reduced glutamatergic concentrations in the anterior cingulate cortex and increased glutamatergic concentrations in the striatum and orbitofrontal cortex [28]. Moreover, both ionotropic glutamate receptors and metabotropic glutamate receptors are linked in virtually every form of learning in the brain, including habit learning [15,29]; are localized in brain circuitry; and are candidates in the pathophysiology of OCD. Several studies show evidence of altered glutamate homeostasis in OCD, with higher levels of glutamate in the cerebrospinal fluid of patients with OCD compared to those of healthy controls [30,31]. Genetics studies suggest an association between polymorphisms of glutamate-associated genes and the development of OCD [32-34]; in particular, OCD in families has been associated with a polymorphism of the gene that codes for N-methyl-D-aspartic acid receptors [32].

Conventionally, guidelines suggest the use of medications that act on serotonergic pathways, such as serotonin reuptake inhibitors (SRIs) and, in particular, selective SRIs (SSRIs), for OCD. Even if the exact mechanisms of their actions remain mysterious, it seems that SRIs exert their effects by influencing CSTC [35]. Unfortunately, it is estimated that around 30% to 60% of patients with OCD do not attain remission after taking SRIs [5]; even when switching to another SSRI, clomipramine, or an atypical antipsychotic, around 30% of patients remain untreated for refractory symptoms.

Given the role that glutamate appears to play in the dysregulation of OCD, glutamatergic drugs could be potential candidates for an OCD therapy augmentation strategy. Glutamate-modulating drugs seem to be potential therapeutic agents for other psychiatric disorders, such as depression, bipolar disorder, and suicidality, that have high comorbidity with OCD [36-38].

In light of the new evidence, several authors have focused their interest on the use of glutamate-modulating agents in patients with refractory OCD. Indeed, some studies that used memantine; riluzole; ketamine; or nutritional supplements, such as inositol and N-acetylcysteine, suggested promising benefits for these kinds of patients [39].

Several randomized controlled trials (RCTs) on the effects of glutamate-modulating drugs on OCD were conducted. A review conducted by Marinova and colleagues [39] showed that memantine seems to have a positive effect on refractory symptoms as an augmentation medication for OCD.

Due to substantial differences in treatment resistance, comorbidity, age, and gender among patients [39], at the moment, it is premature to recommend the use of glutamatergic drugs for refractory symptoms, since more studies are needed to confirm the use of this pharmacological approach for OCD augmentation therapy [40]. Moreover, randomized placebo-controlled trials with larger study populations are necessary in order to draw definitive conclusions on the utility of glutamate-modulating drugs for OCD.

Identifying and confirming the efficacy and safety of new therapeutic approaches for OCD could also be very useful for the purpose of early intervention in patients. Even if there are not sufficient data to support a progression of brain changes, it is likely that early intervention could help to reduce damage resulting from neurotoxicity [41].

### Objectives

The main purpose of our study is to conduct a double-blind, randomized, parallel-group, placebo-controlled, monocenter trial to assess the efficacy and safety of memantine—a low- to moderate-affinity, noncompetitive N-methyl-D-aspartic acid receptor antagonist [40] that is currently approved for the treatment of Alzheimer disease—as an augmentative agent to an SSRI in the treatment of moderate to severe OCD. The second aim of the study is to evaluate the effect of memantine on the concentration and attention abilities of patients with OCD. The third aim is to investigate if responses to memantine could be modulated by variables such as gender, symptoms subtypes, and the duration of untreated illness.

## Methods

This protocol has been reported according to the SPIRIT (Standard Protocol Items: Recommendations for Interventional Trials) statement requirements (Figure 1). The complete SPIRIT checklist is available in Multimedia Appendix 1.

**Figure 1 figure1:**
[figure not shown]
Spirit figure.

### Trial Design

A double-blind, randomized, parallel-group, placebo-controlled, monocenter trial will be conducted over 52 weeks at the outpatient clinic of the Department of Human Neurosciences, Sapienza University of Rome. The study population will include patients diagnosed with moderate to severe OCD according to the diagnostic criteria of the DSM-5 who consecutively access the OCD outpatient clinic of the Department of Human Neurosciences, Sapienza University of Rome. The investigators will be academic research assistants and psychiatrists with experience in OCD.

We will enroll patients who meet the diagnostic criteria of the DSM-5 [12] for moderate to severe OCD, and those with a Yale-Brown Obsessive Compulsive Scale (Y-BOCS) [42] score of >21 will be selected for inclusion in the study. The Y-BOCS, which will be used to evaluate treatment efficacy, is a well-validated, 10-item rating scale that is widely used to measure the severity of OCD symptoms. Participants will be rated with the Y-BOCS at baseline and at 2, 4, 6, 8, 10, and 12 months.

During the screening period and T4 and T6 follow-up visits, all participants will undergo an extensive neuropsychological evaluation. We will assess processing speed by using the Wechsler Adult Intelligence Scale, Fourth Edition, Digit Span [43]; attention by means of the Trial Making Test [44]; computerized alertness and go/no-go task memory by using the Digit and Corsi Span [45], a modified version of the Corsi Block-Tapping Test [46], the story recall portion of the Rivermead Behavioral Memory Test [47], and a modified version of the Babcock Story Recall Test [48]; and executive functions by means of the Stroop task [49], a modified version of the Tower of London test [50], and the Modified Five-Point Test [51].

### Ethical Considerations

The study will be conducted in accordance with the Declaration of Helsinki and its subsequent revisions. Written informed consent will be obtained from all eligible participants, following the complete description of study details. Participants will be informed about their freedom to withdraw from the trial anytime without any negative effect on their therapy. The study was approved for a grant by Sapienza University of Rome (grant RM11916B7477A1B6), approved by the local ethics committee (protocol number: 0784/2022), and registered on ClinicalTrials.gov (trial number: NCT05015595).

Only patients legally capable of giving their consent can participate in the study. The investigator will be responsible for the correctness of the recruitment procedure and will be asked to use comprehensible verbal communication when providing information to the patients. Before entering the study, patients will be fully informed about the purposes of the research; possible benefits; any potential, personal, reasonable risks or discomforts; and the expected duration of their participation in the trial. The investigator will also clearly inform the patients that they can leave the study at any time and for any reason, without giving an explanation, and that discontinuation would not, in any case, deteriorate the patients’ relationship with the physician or the possibility of receiving alternative therapies.

Before recruitment, a copy of the informed consent form and personal data processing consent form will be given to the patients, together with any needed clarification. Sufficient time will be given to enable the patients to decide whether they will participate in the study. Moreover, we intend to also seek approval from the Institutional Review Board of Sapienza University of Rome.

### Participants

The inclusion criteria are as follows: a psychiatrist diagnosis of current moderate to severe OCD based on the DSM-5, a Y-BOCS [42] score of >21, an age of 18 to 55 years, patients in therapy with a stable SSRI for at least 3 weeks prior to enrollment, and written informed consent.

The exclusion criteria are as follows: substance dependence, an IQ of <70, comorbid psychiatric disorders, pregnant or breastfeeding women or women who intend to become pregnant during the period of the study, and concomitant treatments (repetitive transcranial magnetic stimulation, cognitive behavioral therapy, or other glutamate-modulating drugs).

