### Conclusion

To the best of our knowledge, only 4 RCTs have been conducted in recent years that investigated the effects of memantine in patients with refractory severe OCD; our trial will be the first one of its kind in Italy. The innovation of this research proposal is not limited to the evaluation of the efficacy and safety of memantine as an augmentation medication for OCD. Through slow titration and follow-up, we will also observe the minimum effective dose of memantine and its residual efficacy after drug withdrawal by using an 8-week follow-up procedure. In addition, by measuring potential executive function impairments during the study period, we might confirm whether memory and attention are modulators of overall clinical improvement. In other words, we will test if memantine, being an antiglutamatergic agent, acts as a pure antiobsessive medication or if memantine’s ability to improve concentration and attention mimics an antiobsessive effect.

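### The title and abstract call the population refractory OCD, but no inclusion criterion selects for refractoriness, so the trial cannot support a conclusion about refractory patients

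*Protocol article*

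**What the plan says.** Two passages describe this trial's own population as refractory. The title is "Memantine for Refractory Obsessive-Compulsive Disorder", and the abstract's Methods says memantine will be assessed "in the treatment of patients affected by severe refractory OCD". The Conclusion in the Discussion implies the same. It speaks of four earlier trials "in patients with refractory severe OCD; our trial will be the first one of its kind in Italy".

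The passages that set the question and the eligibility do not use the word. The Objectives section studies memantine "as an augmentative agent to an SSRI in the treatment of moderate to severe OCD", and the Objective in the abstract agrees with it. Trial Design says: "The study population will include patients diagnosed with moderate to severe OCD according to the diagnostic criteria of the DSM-5". The Participants section then introduces an explicit list of inclusion criteria:

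- "a psychiatrist diagnosis of current moderate to severe OCD based on the DSM-5"
- a Y-BOCS "score of >21, an age of 18 to 55 years"
- "patients in therapy with a stable SSRI for at least 3 weeks prior to enrollment"
- written consent

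The exclusion list covers substance dependence, low IQ, psychiatric comorbidity, pregnancy and breastfeeding, and certain concomitant treatments. Neither list mentions earlier treatment failure, non-response or refractoriness.

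**The concern.** The population named on the cover is not the one the criteria enrol. A reader of the title or of the abstract's Methods would take the result as evidence in patients whose illness has resisted treatment. The criteria require only that a patient is symptomatic now and has been on a stable SSRI for three weeks or more.

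This matters for the trial's own rationale. The Introduction holds that glutamatergic drugs cannot yet be recommended for refractory symptoms, partly because earlier studies differed in treatment resistance. A trial labelled refractory, with resistance neither defined nor required, would add to that difficulty.

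**Working it through.** The point rests on reading the passages against each other.

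| Place in the article | Population |
|---|---|
| Title | refractory OCD |
| Abstract, Objective | moderate to severe OCD |
| Abstract, Methods | severe refractory OCD |
| Objectives | moderate to severe OCD, added to an SSRI |
| Trial Design | moderate to severe OCD, consecutive clinic patients, Y-BOCS >21 |
| Participants | moderate to severe OCD, Y-BOCS >21, age 18 to 55, stable SSRI for at least 3 weeks |
| Conclusion | refractory severe OCD, said of the four earlier trials; this trial is linked to them by implication |

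**1. What the article means by refractory.** The Background uses the word for the roughly 30% of patients still symptomatic after a change of drug. The Overview in the Discussion ties the rationale to patients who have not responded to standard drug treatment. Both imply a history of failed treatment.

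**2. Whether the criteria imply that history.** Y-BOCS >21 while on an SSRI shows that the patient is symptomatic at entry. Three weeks of stable SSRI sets a minimum on current treatment. Neither separates a patient whose treatment has failed from one whose treatment has recently begun. A patient a little over three weeks into a first SSRI, with a score above 21, meets every listed criterion on these points.

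**3. What the comparison estimates.** Patients are randomised 1:1 within the population the criteria admit. The contrast between arms is valid for moderate to severe OCD (Y-BOCS >21) on a stable SSRI. It carries over to refractory OCD only if the enrolled patients happen to be refractory, which the plan does not secure.

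**4. Illustration only.** The article's sample size can be reproduced for repeated-measures ANOVA, within-between interaction. The inputs from Sample Size are f = 0.25, N = 20, m = 7 measurements, correlation ρ = 0.5 and ε = 1. Alpha is taken as .05, the threshold in Statistical Methods; the .5 printed in Sample Size is a separate matter.

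- Noncentrality: λ = f²·N·m/(1−ρ) = 0.0625 × 20 × 7 / 0.5 = 17.5
- Degrees of freedom: 6 and (20−2) × 6 = 108
- Power: 0.881 at N = 20 and 0.836 at N = 18, so 20 is the smallest balanced total for 0.85, as stated

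Now *assume* that f = 0.25 holds only in refractory patients, that the effect is zero in the rest, and that refractory patients are a share q of those enrolled. Then f becomes 0.25q and λ becomes 17.5q².

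| Assumed q | λ | Power at N = 20 |
|---|---|---|
| 1.0 | 17.5 | 0.88 |
| 0.9 | 14.2 | 0.79 |
| 0.8 | 11.2 | 0.67 |
| 0.6 | 6.3 | 0.40 |
| 0.3 | 1.6 | 0.12 |

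No value of q below 1, and no zero effect in the remainder, comes from the article. The table shows how sensitive the result is to these assumptions and is not an estimate of lost power.

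**The case against.** The strongest reply is that the trial answers the question it formally poses. The Objective in the abstract and the Objectives section both say moderate to severe OCD, and the design and eligibility match them. This stands. A reader might infer that the trial cannot answer its own question; the documents do not support that. Only a conclusion about refractory patients is unsupported.

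Further points also stand, in whole or in part:

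- The Conclusion applies the term to the earlier trials, and the Overview describes four memantine trials as being in moderate to severe OCD. The article uses the terms loosely, and only the title and the abstract's Methods firmly label this trial's population.
- Three weeks is a minimum, stability may refer to dose, and screening may last up to four weeks. Patients early in a first course *could* be enrolled; nothing says that they will be, or how many.
- A reader might infer that continuing SSRI improvement biases the result toward no difference. Improvement common to both arms cancels in expectation from the between-arm difference. The bias would need the further assumption that such patients gain nothing from memantine, or a target redefined as refractory patients. Added variance is plausible but has not been calculated.
- A reader might turn the Background's 30% to 60% non-remission into 40% to 70% who would improve on an SSRI alone. The complement of non-remission is remission, not improvement, and the figure does not describe patients selected for Y-BOCS >21.

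The defence that a journal article condenses the full protocol carries little weight here. The criteria are printed as a list, and that list conflicts with the title.

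**Conclusion.** The contradiction is plain in the article. The refractory label in the title and in the abstract's Methods, echoed in the Conclusion, has no counterpart in the objectives, design or eligibility. Followed as written, the plan gives a valid comparison for moderate to severe OCD with Y-BOCS >21 on a stable SSRI, and no basis for a claim about refractory OCD.

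This conclusion needs no numerical assumption. Its effect on power or on the size of the treatment difference cannot be stated from the documents, because they give neither the refractory share among enrolled patients nor the effect in non-refractory patients. It is an inconsistency to resolve before recruitment, not a failure of the randomised design.

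**What to change.** Reconcile the title, abstract, Objectives, Trial Design, Participants and Conclusion before the first patient is enrolled. The article says recruitment has not started. There are two ways to do this:

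1. Remove the refractory and severe refractory wording from the description of this trial's population, and limit the conclusions to moderate to severe OCD (Y-BOCS >21) on a stable SSRI. This changes wording only and has no recruitment cost.
2. Keep the refractory aim and have the clinical team add its own operational definition of refractoriness to the inclusion list. The cost is an amendment and slower enrolment at a single centre whose Limitations section already blames the small sample on limited service access and the inclusion criteria.

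The choice, and the content of any definition, belong to the sponsor and the clinical team. If power under a mixed population is discussed at all, it should be marked as illustrative.
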